## Abstract

**Background:**

Anatomic short femoral prostheses with a prominent lateral flare have the potential to reduce stress-shielding in the femur through a more physiological stress distribution to the proximal femur. We present the design rationale of a new short uncemented, proximally fixed anatomic femoral implant and the study design of a prospective multi-centre trial to collect long-term patient outcome and radiographic follow up data.

**Methods:**

A prospective surveillance study (trial registry NCT00208555) in four European centres (UK, Italy, Spain and Germany) with a follow up period of 15 years will be executed. The recruitment target is 200 subjects, patients between the ages of 18 and 70 admitted for primary cementless unilateral THA will be included. The primary objective is to evaluate the five-year survivorship of the new cementless short stem. The secondary objectives of this investigation are to evaluate the long term survivorship and the clinical performance of the implant, the impact on the subjects health related Quality of Life and the affect of the prosthesis on bone mineral density. Peri- and postoperative complications will be registered. Clinical and radiographic evaluation of prosthesis positioning will be done post-operatively and at 3, 6, 12, 24, 60, 120 and 180 months follow up.

**Discussion:**

Shortening of the distal stem can maximise bone and soft tissue conservation. New stem types have been designed to improve the limitations of traditional implants in primary THA. A new, uncemented femoral short stem is introduced in this paper. A long-term follow up study has been designed to verify stable fixation and to research into the clinical outcome. The results of this trial will be presented as soon as they become available.

## Background

Although substantial progress has been made in the development of cementless total hip arthroplasty (THA) in recent years, a number of limitations remain. The implantation of the femoral component requires a large surface area of bone to be prepared [1]. Osteopenia due to non-physiological loading and stress protection, distal migration of wear particles from the joint space or inadequate stem fixation can increase the risk of aseptic loosening and subsidence of the stem [2-4]. The use of a stiff femoral component may lead to calcar atrophy and cortical thinning, however modern titanium alloy femoral components appear to reduce the risk of this stress-shielding effect [5,6]. Moreover, intense research efforts have been directed at characterising postoperative thigh pain, a clinical limitation in THA that can range from immediate mild postoperative symptoms to severe disabling pain requiring revision surgery [7,8]. Micromotion, loosening, uneven stress patterns or stem tip sclerosis seem to induce such thigh pain [9,10]. Additionally, the use of a long femoral stem increases the risk of thigh pain due to impingement of the stem tip on the femoral cortex [11] and a direct correlation has been drawn between thigh pain and increased stem sizes [12]. Research has also been conducted into ways to improve the limitations of traditional surgical techniques in THA. A less invasive surgical technique may lead to less pain in the early postoperative period and improve the postoperative functional status [13,14] although the scientific discussion about the superior outcomes of this technique compared with the traditional surgical procedure is still ongoing [15,16].

To address such limitations, new THA implant designs with shorter stems have been developed. Some designs, such as the IPS™ [17], the Mayo Conservative Hip or the Santori Custom stem [18,19] have involved shortening or discarding much of the distal stem with the aim of maximising bone and soft tissue conservation. In addition, anatomic short femoral prostheses can reduce the potential for stress-shielding in the femur through a more physiological stress distribution to the proximal femur [20,21]. An uncemented, anatomic, proximally fixed femoral short stem (the DePuy Proxima™ hip, DePuy International, Leeds, UK) has been designed by a team of international surgeons. The purpose of this study is to conduct a prospective clinical trial to collect long-term clinical, patient outcome and radiographic follow up data. Through the long term follow-up, outcomes measures will be compared to conventional cementless femoral components. The present paper reports on the design rationale of this new short stem prosthesis and the methodological design of the study.

### Proximal load transfer

In 1917, John C. Koch [22] proposed his model of the mechanics of the loading of the hip, which included a geometrical description of the femur and a calculation of stresses induced by load that were assumed to occur during gait. By correlating the stress patterns in the trabecular bone with Wolff's [23] concepts of bone formation, Koch assigned compressive and tensile forces along the medial and lateral femoral surfaces. According to his theory, during femoral loading, the superior neck and proximal lateral three quarters of the femoral shaft were under tensile loading while the distal lateral and entire medial femoral surfaces were under compression. Koch's model was considered as the definitive model of hip biomechanics for the next seventy years and served as a basis for the development, design and validation of THA systems. However, as Koch's static model did not sufficiently focus on the function of soft tissues around the hip joint, Fetto et al. [24] published an advanced model in 1995. Through the inclusion of the iliotibial band as a static lateral tension band and the gluteus medius-vastus lateralis complex as dynamic tension bands along the lateral aspect of the lower limb, the authors demonstrated that compressive loading is actually generated both laterally and medially throughout the femur distal to the greater trochanteric apophysis during the unilateral support phase of gait. Further consistency of this model was achieved by bone morphology studies with cadaveric femora and femoral CT scans, revealing a significant amount of cortical bone mass at the lateral aspect of the femur. The authors therefore concluded that the femoral component of THA prostheses should engage the proximal lateral femoral cortex as an additional area of support against subsidence, to avoid stress-shielding and subsequent loss of proximal femoral bone.

### Lateral flare

Walker at al. [25] discovered fundamental changes in the load transfer between stem and bone when comparing contact pressures between femoral bone and standard length straight stems or stems with a lateral flare. This analysis showed, that for a standard straight stem, loads are mainly transferred through the distal half of the stem (Fig. 1a). In contrast, interface contact stresses from a proximally fixed stem with a lateral flare demonstrated that all of the loading from the prosthesis is transferred to the proximal femur (Fig. 1b). Moreover, the magnitudes of the interface stresses and distal migration during application of the load were both lower in the lateral flare stem. Additionally, results of radiographic follow-up from these authors showed trabecular attachment onto the lateral flare, providing indirect evidence of load transfer in that area. Accordingly, Leali et al. [26] reviewed radiographs from primary THAs with a lateral flare for axial migration and stability. The proximally fixed cementless femoral component showed an average subsidence of 0.32 mm after 2 years, which remained below 1 mm for the duration of the 24–104 month follow-up. The authors concluded that a proximal lateral flare provides significant initial stability, which has been shown to be vital to obtain long-term stability through early bone ingrowth [27]. Additionally, a dual-energy X-ray densitometry study of stems with a lateral flare was performed, which demonstrated that the bone content was preserved at the baseline level or above throughout the follow-up period of 1 year. This was particularly evident in the proximal prosthesis support zones (Gruen zones 1, 2, 6 and 7) [28]. Likewise bone mineral density around the Santori custom short stem was significantly higher in zones 1 and 7 when compared to other conventional cementless implants on a three year follow up [29].

**Figure 1 F1:**
[figure not shown]
Interface contact stresses (MPA) normal to the surface of a straight stem (1a) and a lateral flare stem (1b), in unbonded conditions, without a collar and with zero interface friction.

### Product design

The DePuy Proxima™ hip (DePuy International, Leeds, UK) is manufactured from titanium alloy (Ti-6AL-4V) and has a lateral flare intended to conform to the lateral femoral endosteal surface (Fig. 2). The stem has a 12/14 taper and is available in high and standard offsets. The physiological neck angle is set at 130° and the prosthesis is anatomically shaped with an anteverted neck and available in left and right versions. The entire proximal region of the stem has a sintered bead porous coating with a thin layer of Hydroxyapatite for optimized rapid osseointegration and is stepped to minimise shear forces.

**Figure 2 F2:**
[figure not shown]
The DePuy Proxima™ hip.

### Surgical technique

Femoral components with a significant lateral flare should be implanted with modified surgical insertion technique, to minimise the potential risk of damage to the greater trochanter [18]. Instruments and implants are therefore first inserted in a slight varus position and then rotated into the correct axial alignment. Adequate cancellous bone for osseointegration should be left on the lateral part of the femur whilst moving distally in the femoral metaphysis. Initially a high neck cut is used, as preservation of the femoral neck has been shown to provide an effective means to achieve immediate, post-operative torsional and coronal stability, which is a key factor in the prevention of loosening of the femoral component of THA [30,31]. Biomechanical stability of the new implant was intensively tested and compared to other clinically successful shaft prostheses prior to the start of the clinical study [32,33].

## Methods

### Study design

This is a multi-centre, prospective, post marketing surveillance study with a follow up period of 15 years (ClinicalTrials.gov Identifier: NCT00208455). It will be open, non-randomised and non-stratified. The primary objective is to evaluate the five-year survivorship of the new cementless short stem. The secondary objectives of this investigation are to evaluate the long-term survivorship and the clinical performance of the implant, the impact on the subjects health related Quality of Life and the affect of the prosthesis on bone mineral density.

### Study population

The study will be conducted in four centres (UK, Italy, Spain and Germany). The recruitment target is 200 subjects, with each centre recruiting 50 subjects. The study has been approved by the ethics committees of Southmead LREC (Bristol, UK), Ospedale San Pietro (Rome, Italy), Hospital Arnau de Vilanova (Valencia, Spain) and University of Regensburg (Regensburg, Germany). Patients included will be aged between 18 and 70 years, suitable for a cementless primary THA and able to understand the study and co-operate with the study follow up visits. The main primary diagnosis will be osteoarthritis. However, other diagnoses will be included such as rheumatoid arthritis, avascular necrosis, developmental dysplasia of the hip or fractures. Excluded patients will be those with other conditions or disorders, unrelated to their hip replacement, that would affect their long-term involvement in the study and patients already participating in other research studies. Only one hip per patient is entered into the study. Patients undergoing a simultaneous bilateral or with a problematic or recent contralateral hip replacement will also be excluded.

### Intervention

Cementless total hip replacements using the DePuy Proxima™ hip component.

### Measurements

#### General measurements

The Harris Hip Score will be used to assess the clinical outcomes. The Oxford Hip Score will be used to assess the patient related outcomes. The effect of the implant on bone mineral density will be assessed using DEXA analysis.

#### Perioperative measurements

Demographic information such as height, weight and age will be collected pre-operatively. In addition information concerning the condition of the operative joint, primary diagnosis, medical history and concomitant medical problems will be collected. The Charnley and DORR classifications will be used to assess the pre-operative joint. Baseline Harris Hip and Oxford Hip scores will also be completed. Intra-operatively, surgical approach, average surgical time, incision length, blood loss and details of any operative complications will be recorded.

#### Radiographic evaluation

Radiographic evaluations will be done post-operatively and at 3, 6, 12, 24, 60, 120 and 180 months follow up. At each time-point standard AP and Lateral x-rays will be taken and assessed. For the femoral implant signs of radiolucency and osteolysis will be recorded if observed and subsidence will be assessed by recording the position of the component at successive time-points. In addition, evidence of positive bone response will be recorded. Given the lack of a distal portion the Gruen zones have been adapted (Fig. 3). For the acetabular component, evidence of osteolysis or resorption will be recorded, any change in position or orientation will be covered and wear will be measured if possible.

**Figure 3 F3:**
[figure not shown]
Adapted Gruen zones.

### Statistical analysis

The survivorship will be calculated using both revision and radiological loosening of the implant as end-points for the analysis. Kaplan-Meier survivorship curves will be calculated. Analysis will be performed to assess whether the patient or surgical characteristics have any affect on the primary endpoints. In addition, multivariate analysis using Cox's Proportional Hazards modeling will be undertaken in relation to the survival analysis.

The statistical analysis will be performed by a qualified Biostatistician ([name], DePuy International, Leeds, UK) using the statistical package SAS Version 8 (SAS Institute Inc., [name]) and Microsoft Access. All significance tests will be two-sided and carried out at a 5% significance level, 95% confidence intervals will be regarded as appropriate.

All eligible subjects admitted to the study that receive treatment, and have at least one usable post-treatment assessment, will be included in the statistical analysis where possible. Protocol violators will not be included in the statistical analysis. If applicable, the number of ineligible subjects that received treatment and the reasons for ineligibility will be summarised.

Missing values will be excluded from the analysis as they will be assumed to be missing completely at random and so no loss of information or bias will occur if they are not included in the analysis. If more than 20% of values are missing for a particular analysis variable, then this may significantly bias the results, hence further statistical investigation methods may be employed to try and investigate the effect of missing values.

Subjects who withdraw or are lost to follow-up will be included in the analysis up to the point of withdrawal or last known assessment.

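### Loosening that starts after the 24-month film is first seen at the 60-month film, so an ordinary Kaplan-Meier five-year figure for that end-point depends on when the film is taken

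*Protocol article*

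**What the plan says.** Under Study design the article sets the target: "The primary objective is to evaluate the five-year survivorship of the new cementless short stem". Under Radiographic evaluation it gives the film schedule: "Radiographic evaluations will be done post-operatively and at 3, 6, 12, 24, 60, 120 and 180 months follow up". Under Statistical analysis it names two end-points: "The survivorship will be calculated using both revision and radiological loosening of the implant as end-points for the analysis". It does not say whether they form one composite or two curves.

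The methods named are "Kaplan-Meier survivorship curves will be calculated" and "multivariate analysis using Cox's Proportional Hazards modeling will be undertaken in relation to the survival analysis". The censoring rule reads: "Subjects who withdraw or are lost to follow-up will be included in the analysis up to the point of withdrawal or last known assessment". That rule covers withdrawals and losses. The article does not say how hips still in follow-up are treated at a data cut. On size, it says: "The recruitment target is 200 subjects, with each centre recruiting 50 subjects".

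**The concern.** A revision has a date. Radiological loosening does not: all that is known is that it arose between the last clear film and the first film showing it. Such times are interval-censored, whereas ordinary Kaplan-Meier and Cox need the event time itself or a right-censored time.

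The mismatch matters most where the gap between films is long and the curve is read at its edge, which is the case here. A stem that loosens at month 30 and is filmed at month 61 counts as surviving at five years. The same stem filmed at month 59 counts as failed.

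The study has no comparator arm, so the survivorship percentage is its main result. If true failure is a few per cent, a shift of one to three points is a large share of the reported failure rate. The five-year figure could also change between reports with no change in any patient's five-year status.

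**Working it through.** The article states no survivorship rate, event count or precision, so there is no figure of its own to reproduce.

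**Inputs from the article.** Films at 3, 6, 12, 24, 60, 120 and 180 months, giving gaps of 3, 3, 6, 12, 36, 60 and 60 months; 200 hips (4 × 50); primary time point 60 months; Kaplan-Meier.

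**Assumptions, not in the article.** True five-year loosening of 5% (range 3 to 10%); constant hazard; loosening dated on the actual film date; 60-month films either spread evenly over months 57 to 63 or taken 1 to 3 months late.

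**Step 1: how much loosening falls in the long gap.** The monthly hazard is λ = −ln(0.95)/60 = 0.000855. Survival at 24 months is exp(−24λ) = 0.9797. The share of five-year loosening that starts between months 24 and 60 is (0.9797 − 0.9500)/0.05 = 0.59.

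**Step 2: Kaplan-Meier at 60 months, loosening only, hips still at risk afterwards.**
- All films by month 60: all the loosening has been counted, giving 95.0%.
- Half the films after month 60: 1 − [0.0203 + 0.5 × 0.0297] = 0.965.
- All films after month 60: only loosening found by the 24-month film is counted, giving 98.0%.

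| True five-year survivorship | All films by month 60 | About half after | All after |
|---|---|---|---|
| 97% | 97.0% | 97.9% | 98.8% |
| 95% | 95.0% | 96.5% | 98.0% |
| 90% | 90.0% | 92.9% | 95.9% |

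**Step 3: a five-year data cut with each sound hip censored at its own film.** With films spread over months 57 to 63, hips leave the risk set at rate 1/(63 − u), and the integral from 57 to 60 is ln 2 = 0.693. Films before month 60 fall on average at 58.5 months, 34.5 months after the previous film, and find 1 − exp(−34.5λ) = 0.0291 loose. Kaplan-Meier at 60 months is then 0.9797 × exp(−0.0291 × 0.693) = 0.960.

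**Step 4: simulation.** With 200 hips and a true value of 95.0%, the 60-month estimate averages 96.0% at a five-year cut, 96.5% once ten-year films are in, and 98.0% with films 1 to 3 months late. These agree with Steps 2 and 3. If all films fall in months 57 to 60 and sound hips are censored at their own film, the risk set empties as events occur. The 60-month mean then drops to 82% (median 88%). It returns to 95.1% when later follow-up keeps the hips at risk.

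**Step 5: sensitivity.** Adding unrelated revision (2%) and dropout (10%) by five years makes the true value 93.1%. The estimate is 92.9 to 93.1% with films on time, 94.6% with a ±3-month spread and 96.1% with late films. Across 3 to 10% loosening and constant or decreasing hazard, the overstatement is about 0.7 to 3.3 points with spread films and 1.4 to 5.9 points with late films.

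**Step 6: the alternative.** Assigning each film to its nominal interval gives 94.9 to 95.0% against a true 95.0% for ±3 and ±6 month spreads. With films on average two months late it also counts loosening up to about month 62, so the figure is 0.95 × exp(−2λ) = 94.8%, an error of 0.2 points. An interval-censored model was not fitted.

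**The case against.** This is a condensed article. Visit windows, the rule for dating loosening and the time at which the curve is read commonly sit in the full protocol or SAP, which are not shown. If loosening is dated at the nominal visit, Kaplan-Meier gives 95.0% against 95.0% and the problem disappears. All of this stands: the absence of a window or dating rule is not itself a fault, and the error is conditional. What remains is that the article names an estimator for exact event times, for an end-point seen only at visits, and reads it at the visit that closes the longest gap before five years.

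The size can also be disputed. The sampling standard error is √(0.05 × 0.95/200) = 1.5 points, so a shift of 1.0 to 1.5 points is no larger than chance variation. If 70% of five-year loosening occurred by month 24 (an assumption), the ±3-month figures would be 95.5% and 95.9%. Both points are fair. But this is a systematic shift that the confidence interval does not cover, and with late films it is about twice the standard error.

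A reader might infer four stronger points that the article does not support:
- *That loosening is seen only at films 36 to 60 months apart.* Up to month 24 the gaps are 3 to 12 months. One 36-month gap precedes the primary time point, and the 60-month gaps affect only long-term survivorship, a secondary objective.
- *That the five-year figure is certainly biased.* It is essentially right if films fall by month 60 and hips stay at risk.
- *That the curve collapses to about 82% at the end of a ±3-month window.* That is a 63-month reading driven by the last few hips, at a data cut the article does not state. With later follow-up the 63-month value is 95.0%.
- *That revision is treated as censoring for loosening.* This needs a separate loosening-only curve, which the article does not specify.

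**Conclusion.** The point holds in conditional form and concerns only end-points that include radiological loosening. If loosening is dated on the film date, the five-year figure depends on appointment timing. At 5% true loosening, reported failure would be about 3.5 to 4.0% with a ±3-month spread and about 2% with films 1 to 3 months late. The usual direction is to make the stem look better. The exception is a five-year cut with hips censored at their own film, where early films can push the figure too low. Whether that censoring would be used is unknown, because the stated rule covers withdrawals and losses only.

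The sizes rest on the assumed loosening rate, hazard shape and film timing. The structure rests on the article alone: its schedule, primary time point and named methods. The revision-only curve is not affected if revision dates are recorded. The Cox model would use the same film-dated times, but its error was not quantified.

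**What to change.** For any end-point that includes radiological loosening:
- Count stem revision as a failure at its recorded date, and loosening as a failure in the interval from the last clear film to the first film showing it.
- Estimate five-year survivorship with an interval-censored (Turnbull) estimator or a life table on nominal visit intervals. Assign the 60-month film to the five-year interval whatever its actual date. With Turnbull, say in advance where the curve is read, because intervals that straddle month 60 leave the value at exactly 60 months undetermined.
- State how hips still in follow-up are handled at a data cut.

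Keep ordinary Kaplan-Meier for revision alone. A discrete-time (grouped) model for covariates on loosening is a reasonable option but not essential.

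The cost is a change of analysis wording, modest programming and possibly slightly wider confidence intervals. With late films, the life table also counts the little loosening that arises between month 60 and the film. No extra visits or films are needed.

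### Requiring a usable post-treatment assessment for the survivorship analysis can drop known early revisions; any material bias in the five-year figure is then upward

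*Protocol article*

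**What the plan says.** Under Study design the article states: "The primary objective is to evaluate the five-year survivorship of the new cementless short stem". The Statistical analysis section gives the endpoints, "The survivorship will be calculated using both revision and radiological loosening of the implant as end-points for the analysis", and the estimator, "Kaplan-Meier survivorship curves will be calculated".

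The same section then defines who is analysed. Subjects must be eligible, must have been treated "and have at least one usable post-treatment assessment, will be included in the statistical analysis where possible". The rule is written for the statistical analysis as a whole. It does not distinguish survivorship from the scores, and it does not define a usable assessment.

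Two other statements bear on it:

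- Radiographic evaluation: "Radiographic evaluations will be done post-operatively and at 3, 6, 12, 24, 60, 120 and 180 months follow up". The first film is therefore taken after the operation and the next scheduled one at 3 months.
- Statistical analysis, last sentence: "Subjects who withdraw or are lost to follow-up will be included in the analysis up to the point of withdrawal or last known assessment". This does not say what happens to a subject who leaves before any usable assessment. Read alone it keeps that subject; the inclusion rule leaves that subject out.

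**The concern.** A condition of at least one assessment after treatment is reasonable for the Harris and Oxford scores, radiographic signs and bone density, where a subject without a measurement has nothing to contribute. Revision is different. It can be known without any study assessment, and follow-up starts at implantation.

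Applied to survivorship, the rule makes entry depend on an event after time zero, and an early revision can prevent that event. A subject revised before a usable assessment is a known failure of the study stem, yet the wording leaves that subject out of both numerator and denominator. The restriction brings the survivorship analysis no benefit in return, since Kaplan-Meier already handles short follow-up by censoring. Complications in the same subjects would leave their tabulations too.

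At stake is the primary figure of an uncontrolled study. The Discussion names primary and torsional stability as a major concern for short stems, so early failures should not depend on an undefined word for their inclusion.

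**Working it through.** **Inputs.** Four centres with 50 subjects each (Study population): 4 × 50 = 200, which reproduces the recruitment target. The article gives no expected survivorship, precision, early-revision count or loss rate. All event and loss counts below are assumptions.

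**Step 1: early revisions dropped, no other losses.** With d failures by five years among N subjects, survivorship is 1 − d/N. If k early revisions are left out it becomes 1 − (d − k)/(N − k). The shift is k(N − d) / [N(N − k)].

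Example with N = 200, d = 10, k = 1: 1 × 190 / (200 × 199) = 0.48 point.

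| Assumed failures d | All treated | k = 1 | k = 2 | k = 4 |
|---|---|---|---|---|
| 6 | 97.0% | 97.5% (+0.49) | 98.0% (+0.98) | 99.0% (+1.98) |
| 10 | 95.0% | 95.5% (+0.48) | 96.0% (+0.96) | 96.9% (+1.94) |
| 20 | 90.0% | 90.5% (+0.45) | 90.9% (+0.91) | 91.8% (+1.84) |

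As failure proportions: with 10 failures (5.0%), dropping 1, 2 or 3 gives 9/199 = 4.5%, 8/198 = 4.0% or 7/197 = 3.6%. With 4 failures (2.0%), dropping 1 or 2 gives 3/199 = 1.5% or 2/198 = 1.0%.

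**Step 2: only event-free early losses dropped.** Suppose 10 subjects leave without an event before the first usable assessment.

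- If they leave before the first revision, they are in no risk set at an event time and removing them changes nothing.
- If they leave just before 3 months, after 4 revisions that are kept, with 6 later failures, the full estimate is (196/200) × (180/186) = 0.9800 × 0.9677 = 94.84%. Without the 10 losses it is 180/190 = 94.74%, which is 0.10 point lower.
- With 1 earlier revision kept and 9 later ones: (199/200) × (180/189) = 94.76% against 180/190 = 94.74%, about 0.02 to 0.03 point lower.

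Over 6, 10 and 20 assumed failures, with 1 to 4 early revisions kept, the fall is 0.02 to 0.10 point.

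**Step 3: both groups dropped.** Take 10 failures, 4 of them early, and 10 losses just before 3 months. The full estimate is 94.84%. After the rule it is 180/186 = 96.77%, a rise of 1.94 points. If the losses come before the first revision, the full estimate is 180/190 = 94.74% and the rise is 2.04 points. Removing the losses as well hardly changes the result of Step 1.

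**Step 4: the post-operative film counts as usable.** Almost every implanted subject then qualifies, almost nobody is removed, and the shift is close to zero.

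**Comparison.** The smallest rise for one dropped revision (0.45 point) is more than four times the largest fall found in Step 2 (0.10 point).

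**The case against.** The strongest reply is that the rule removes almost nobody. A post-operative film is scheduled and assessed for each subject, so on a natural reading each implanted subject has an assessment after treatment. A dropped revision would then require a missing or unreadable film, a revision before the next visit, and a decision that the documented revision is not itself usable information. The words *where possible* might also be read as leaving room for inclusion. This reply stands as a limit on the size. It does not remove the point, because the text does not say whether that film, or the contact at revision, meets the condition.

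A reader might also infer that the rule can delete only early revisions and can therefore only flatter the stem. The documents do not support that. The rule equally removes subjects who die, withdraw or are lost without an event, whom the sentence on withdrawals would otherwise keep until they leave. As Step 2 shows, removing them can lower the estimate very slightly. Nor does the article support the inference that every revision before 3 months is lost, or that stability failures must come early: the Discussion raises stability as a concern but gives no timing.

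The event counts are hypothetical. With 10 failures in 200, the 95% interval is about ±3 points (1.96 × √(0.05 × 0.95/200) = 3.0), so one dropped revision is small beside sampling error. That is true, but an interval computed on the reduced set does not allow for the shift.

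Finally, a condensed article may leave definitions to a fuller plan. That excuses the missing definition of usable. It does not excuse a stated rule that covers the primary analysis without exception.

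**Conclusion.** The point holds in a limited form. As written, the inclusion rule covers the primary survivorship analysis, is not needed there, and can exclude known early revisions. Any material bias is then upward: about 0.5 percentage point of five-year survivorship per dropped revision at N = 200, and about 2 points for four. These sizes rest on assumed counts of 6, 10 or 20 failures.

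The effect of also losing event-free subjects is nil or very slightly downward. The total effect is near nil if the immediate post-operative film qualifies as usable, and it is nil if no early revision lacks a usable assessment. The article settles neither question. The change is worth making because the wording affects the primary figure and is easily corrected, not because a large bias has been shown.

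**What to change.** Replace the single rule with two:

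- *Survivorship and complications are analysed in all subjects in whom the study stem was implanted, from the date of surgery, with no requirement for a later assessment. Subjects lost early are censored at their last known status.*
- *The condition of at least one usable assessment after treatment applies only to the Harris, Oxford, radiographic-sign and DEXA summaries.*

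Delete *where possible*. The first sentence also resolves the tension with the statement on withdrawals and losses.

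The cost is a change of wording in the analysis-set definition. It needs no new data or visits, because the surgery and revision dates are required for the survivorship analysis in any case. The only downside is a possibly less favourable figure.
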